## **8.1. Sample Size Estimation**

No formal statistical hypothesis testing is planned for this study due to the exploratory and descriptive nature of the study. All subject data will be listed. All analyses will be descriptive, providing summary statistics (number of observations, arithmetic mean, standard deviation, minimum, median and maximum) for quantitative data, and frequency tables (absolute and relative frequencies) for qualitative/ordinal data.

For Part A, the sample size of 4 subjects with a randomization ratio of 3:1 is chosen to balance the need to maximize information on the niclosamide solution and the need to have a placebo subject to blind the study. Placebo subjects in Part A will be pooled, if appropriate.

Four subjects (in a crossover design) in Part B seems large enough to compare the two different niclosamide formulations and to get preliminary safety data of and PK data of the new oral solution.

Eight subjects on verum (together in the low and high dose group) seems large enough to have an adequate safety and PK data set in a multiple dose setting (Part C) considering the preliminary PK and safety data from Part A of this study.

A more technical and detailed elaboration of the statistical analysis will be included in a separate Statistical Analysis Plan (SAP).

## **8.2. Analysis Sets**

For all analysis sets, subjects will be analyzed according to the study treatment received.

- The safety analysis set will include all subjects that received any study drug.
- The PK analysis set will include all subjects with at least one available valid PK concentration measurement, who received any study drug and with no protocol deviations that impact on PK data.
- Per protocol analysis set: Defined as all subjects completing the study without major protocol deviations

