Currently, Part C is designed as a single arm MD safety and tolerability study for the Niclosamide/Camostat combination treatment. The combination is no longer needed to be tested (see above). Instead, it is proposed to have a 3 group MD study on niclosamide solution. Evaluation of Part A of the study has revealed that drug administration might result in liquid stool or even diarrhea. Even though clinically mild, these symptoms might have a severe impact on the therapy if correlated with reduced absorption of the active substance. The symptoms might be either due to the active substance or, more likely, to the excipient. PEG 400 is known to cause diarrhea and PEG formulations are indeed clinically used as laxatives. PEG is not absorbed but resides in the gastro-intestinal tract. It might therefore accumulate in subjects with a stool frequency less than 24 hours (administration frequency). Therefore, even though the 1600 mg dose is well-tolerated, and the active substance is unlikely to accumulate (half-life 4-5 hours), the excipient might accumulate, and the treatment might need to be discontinued. Therefore, a second dose arm of 1200 mg, containing 25% less PEG, will be tested in parallel to compare bioavailability over the course of the treatment (7 days). Based on the PK data from study Part A, 1200 mg niclosamide solution is estimated to still reach therapeutic plasma levels. The dose group of 1600 mg will be stopped if intolerable GI side effects occur. If the SMC and Investigator agree (after

reviewing the safety data), subsequent subjects in the 1600 mg dosing group will be dosed with 1200 mg niclosamide solution.

5) Part C will run in parallel with Part B

The current protocol foreseen submission of a substantial amendment after Part A and after Part B in order to start Part B and C, respectively.

It is now proposed to run Part B and C in parallel. Since Part B is only an extension to Part A3 plus (1600 mg under fed conditions) with the additional goal to investigate the relative bioavailability of the new niclosamide solution with the approved chewing tablets, there is no additional safety data to be expected from Part B for Part C. Therefore, both parts can now be run in parallel.

The following changes to the protocol have been implemented:

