### **Part C: Multiple dose part with the niclosamide solution**

The multiple dose part (Part C) will start in parallel to Part B since Part B will only be performed to get information about the relative bioavailability of the niclosamide solution compared to the approved niclosamide chewing tablets. The chosen dose of the niclosamide solution in Part B is identical with the highest dose given under fed conditions in Part A of this study, which was safe and well tolerated. Thus, there is no additional risk to start with Part C in parallel to Part B.

Part C is comprised of a screening visit (between Day -21 and Day -2), a baseline evaluation (Day -1), a multiple dose treatment period (Day 1 through Day 7, discharge on Day 8) with OD dosing of niclosamide solution and one EOS visit between Day 10 and Day 12.

Part C consists of three parallel groups:

Group 1: 1200 mg niclosamide solution (n=4)

Group 2: 1600 mg niclosamide solution (n=4)

Group 3: Placebo (n=4)

The high dose of niclosamide solution can be stopped and continue with the medium dose in the subsequent subjects, if moderate to severe GI side effects occur most likely due to an accumulation of the excipient PEG-400 in the gut.

Approximately 12 subjects (4/group) will be enrolled in this part of the study, who receive the niclosamide solution (1200 mg and 1600 mg QD) or placebo over a treatment period of 7 days. The dose of the niclosamide solution depends on the safety and PK results of Part A and will not exceed 1600 mg QD.

Subjects will remain domiciled in the study site from Day -1 until the Day 8 (24h post dose) and until all assessments have been completed. Subjects will be allowed to leave the study center on Day 8 at the discretion of the Investigator, if there are no prohibitive safety findings. The subjects will be asked to return to the study site for the EOS assessments on Day 10 (+2 days). The EOS evaluation has also to be performed if a subject prematurely terminates the study for any reason.

All baseline safety evaluations results must be available prior to dosing.

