### Part B (relative bioavailability compared to chewing tablets)

Planned doses:

- Single dose of 1600 mg oral niclosamide solution (highest dose that was tested to be safe and tolerable in Part A) under fed conditions
- Single dose of 2000 mg niclosamide chewing tablets as multiples of 500 mg chewing tablets under fed conditions

Part C (multiple doses of the niclosamide solution)

- Multiple doses of 1200 mg oral niclosamide solution under fed conditions over 7 days
- Multiple doses of 1600 mg oral niclosamide solution under fed conditions over 7 days
- Placebo under fed conditions over 7 days

In all cohorts, study drug will be administered at the study site.

In Part A cohorts, subjects must have fasted overnight for at least 9 hours before study drug intake. Intake of water is not allowed from approximately 2 hours before until approximately 2 hours after study drug intake (except for the non-carbonated water required for study drug intake). Standard lunch will be served within 15 to 30 minutes after the 4-hour PK sampling on Day 1 and in Part B also on Day 3. The lunch should be of the same composition for all subjects on Day 1. The standard lunches should be ingested entirely within 30 minutes. If this is not possible, the approximate percentage of the consumed food should be documented.

A standard snack and a standard dinner will be served approximately 7 and 10 hours postdose, respectively. This snack and dinner should be of the same composition for all subjects.

In the fed dose cohort in Part A (cohort 3) and in Part B and Part C, following overnight fast of at least 9 hours, subjects should start a high fat meal 30 minutes prior to the study drug administration at the study site between 7.30 and 10.00 AM. This meal should contain approximately 800 to 1000 calories and should derive approximately 150, 250, and 500 to 600 calories from protein, carbohydrate, and fat, respectively (according to the FDA guidance for industry). Subjects should consume the entire meal within 30 minutes. If this is not possible, the approximate percentage of the consumed food should be documented. Within 10 minutes after completing breakfast, but no more than 30 minutes from the start of their high fat meal, study drug will be administered with approximately 240 mL of non-carbonated water. Thereafter, subjects should receive standardized meals scheduled at the same time in each cohort of the study.

[figure not shown]

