## **8.3. Protocol Deviations and Handling of Missing Values**

Data from subjects who prematurely terminate the study will be used up to the maximum extent possible.

All protocol non-compliances will be listed and the reasons for exclusion of subjects from any of the analysis sets will be listed. Where relevant, the data from these subjects will be described separately.

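### The PK analysis set drops a whole subject for any PK-relevant deviation, so a problem confined to one dose also takes unaffected profiles out of summaries of three or four subjects

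*Protocol*

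**What the plan says.** Protocol section 8.2 opens the PK set widely and then narrows it. "The PK analysis set will include all subjects with at least one available valid PK concentration measurement" is the entry condition, and the same sentence restricts it to those "who received any study drug and with no protocol deviations that impact on PK data". The unit throughout is the subject. No dose, day, profile or period is mentioned. Section 8.3 uses the same unit: it requires reasons to be listed for leaving subjects, not samples, out of an analysis set.

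Section 3.1 gives Part C four subjects in each of three groups, dosed once daily for seven days. Table 3 schedules full concentration profiles on Days 1 and 7 and a trough on each of Days 2 to 6. Every Part C dose falls under a meal and timing limit (section 6.1.1): "Within 10 minutes after completing breakfast, but no more than 30 minutes from the start of their high fat meal, study drug will be administered". Cohort A3 has four subjects at 3:1, so three on niclosamide, each dosed once fasted and once fed.

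**The concern.** A multiple-dose or two-period design gives several largely separate pieces of PK information per subject. A deviation at one dose usually spoils one of them. Under section 8.2 as written, it removes all of them from the PK set. The sentence is also at odds with itself. It accepts a subject with a single valid concentration, so partial data are good enough to enter, but it rejects a subject with two dozen valid concentrations and one affected day.

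At stake are the descriptive PK summaries in very small groups: the Day 1 and Day 7 parameters at each Part C dose, and the fasted 1600 mg summary in A3, which belongs to the primary PK objective in section 2.1.1. Replacement in section 3.1.1 covers drop-outs, so a completer who is excluded for a deviation is not clearly replaced.

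**Working it through.** **Inputs.** Group sizes: section 3.1. Sampling: Table 3 (10 time points on each full-profile day; troughs on Days 2-6). Half-life 4-5 h: rationale of Amendment 2. Section 1.3 agrees that accumulation is not expected. The protocol gives no deviation rate, so any rate below is an assumption.

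**The plan's own figure.** Section 8.1 counts eight Part C subjects on active drug: 4 + 4 = 8, which agrees with section 3.1. There is no power calculation to reproduce.

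**1. What one exclusion removes.** Per Part C subject: 2 × 10 + 5 = 25 scheduled samples, or 24 if the Day 1 24 h sample is also the Day 2 trough. Both profiles and all troughs go.

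**2. How far a one-dose deviation reaches.**
- Accumulation ratio for once-daily dosing = 1/(1 − 0.5^(24/h)). For h = 4 this is 1/(1 − 0.0156) = 1.016. For h = 5 it is 1/(1 − 0.0359) = 1.037. So about 2-4%.
- The Day 1 profile ends at 24 h, so a deviation on Day 3 or later comes after it.
- The share of a Day 3 dose effect left at the Day 7 dose, 96 h later with h = 5, is 2^(−96/5) = 1.7 × 10⁻⁶. For a Day 5 dose, 48 h earlier, it is 2^(−48/5) = 0.0013, or 0.13%.

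A mid-week deviation confined to one dose therefore leaves both profiles materially intact. What it can touch is the trough or troughs that follow.

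**3. Cost per exclusion.** Part C: 1/4 = 25% of a dose group. A3: 1/3 = 33% of the active subjects. The 90% confidence half-width for a mean, in SD units, is t(0.95; n−1)/√n. For n = 4 it is 2.353/2 = 1.18. For n = 3 it is 2.920/1.732 = 1.69. The ratio is 1.43.

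**4. How often, under an assumption.** Let p be the chance of a PK-relevant deviation per dose, independent over seven doses. P(subject excluded) = 1 − (1 − p)^7.

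| p (assumed) | Subject excluded | Expected kept of 4 | All four kept | One given profile lost if exclusion is by profile |
|---|---|---|---|---|
| 2% | 13% | 3.5 | 57% | 2% |
| 5% | 30% | 2.8 | 24% | 5% |

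**5. Cohort A3.** The fasted dose comes first, so a fed-period deviation cannot change the fasted profile. The food-effect model in section 8 needs evaluable data from both periods and loses this subject under either rule. The descriptive fasted summary does not need the fed period, but loses the subject as well under the rule as written.

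**The case against.** The strongest case against the point is that little is truly lost. Section 8.1 says all subject data are listed, and section 8.3 provides for separate description of excluded subjects where relevant. Only deviations judged to affect PK count, and subjects are domiciled and dosed at the site, so such deviations may be rare. The study is descriptive with no hypothesis test. The protocol does not say which set each PK table uses, and it leaves technical detail to an SAP that is not at hand. All of this stands and limits the weight of the point. It does not remove it: section 8.2 states a rule rather than leaving a gap, and an SAP that excluded only affected samples would depart from that rule.

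Three stronger readings are tempting and are not supported.
- A reader might infer that the data are deleted. They leave the PK-set summaries, not the report.
- A reader might infer from "Data from subjects who prematurely terminate the study will be used up to the maximum extent possible" that drop-outs are treated more generously than completers with a deviation. That sentence does not exempt drop-outs from the deviation clause in section 8.2, which applies to both.
- A reader might infer that subjects with gastrointestinal symptoms would be excluded, hiding the loss of absorption behind the Part C redesign (Amendment 2: "these symptoms might have a severe impact on the therapy if correlated with reduced absorption of the active substance"). But symptoms are adverse events, not protocol deviations. Sections 4.7 and 6.1.1 ask only that an unfinished meal be documented, and neither names it as a ground for exclusion. Such a link is possible, but nothing in the text establishes it.

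**Conclusion.** The point holds as a weakness in a stated rule. Followed literally, section 8.2 removes unaffected profiles from the PK-set summaries because of a deviation elsewhere in the same subject's data. The firm size is 25% of a Part C dose group or 33% of the active subjects in A3 for each subject excluded, with a 90% interval for a mean about 1.4 times as wide when four become three (equal SD assumed). The frequency is not known. The 13-30% of Part C subjects rests on an assumed 2-5% per dose and independence between days.

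The claim that both Part C profiles survive a mid-week deviation rests on the 4-5 h half-life and on a deviation confined to one dose. A longer-acting deviation could affect more samples. No stated figure in the protocol is wrong. This is worth correcting because the groups are so small, but it does not threaten the study.

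**What to change.** Amend section 8.2, and align the SAP, so that:
- the PK set contains every subject who received niclosamide and has at least one valid concentration;
- a PK-relevant deviation excludes only the concentrations or the profile that it affects, and the subject's other days and periods stay in;
- these decisions are made before unblinding or, in open-label Part B, before the PK results are reviewed.

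Optionally, add one summary with nothing excluded. The completeness condition for the food-effect and relative bioavailability models in section 8 can stay as it is.

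The cost is one amended sentence and an exclusion flag per sample or profile. The downside is that the number of subjects varies by day or period within a group, so each table must show its own n.

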## **8.3. Protocol Deviations and Handling of Missing Values**

Data from subjects who prematurely terminate the study will be used up to the maximum extent possible.

All protocol non-compliances will be listed and the reasons for exclusion of subjects from any of the analysis sets will be listed. Where relevant, the data from these subjects will be described separately.

# **9. General Study Conduct Considerations**

## **9.1. Regulatory and Ethical Considerations**

The trial will be carried out in compliance with the protocol, the ethical principles laid down in the Declaration of Helsinki, in accordance with the ICH Harmonized Tripartite Guideline for Good Clinical Practice (GCP), and other relevant regulations.

[figure not shown]

## **9.2. Informed Consent**

Prior to performing any other study-related procedure, each potential subject must provide signed acknowledgement of their freely given informed consent. Either the investigator or a designated person will explain the aims, methods, anticipated benefits and potential hazards of this protocol and any discomfort it may entail. A corresponding written explanation will also be provided (informed consent form; ICF) and the subject allowed sufficient time to consider the information.

Prior to signing the consent form, the subject will be given an opportunity to discuss any issues concerning this protocol with a physician who has suitable knowledge of the procedures involved and to have all questions answered openly and honestly.

If the subject is willing to participate, the ICF will be signed and personally dated by the subject and the physician taking the consent. The subject will receive a signed copy.

## **9.3. Protocol Amendments**

Any significant change in the study requirements, design or scheduled activities requires a protocol amendment to be issued. The investigator must not make any changes to the study or deviate from this protocol without competent regulatory authority(s), ethical committee and sponsor approval, except when necessary to avoid immediate danger to subjects. A change in procedures specified in this protocol that is intended to remove an immediate danger to subjects may be implemented immediately. The change must be documented and reported to the ethical committee and the appropriate regulatory authority(s). An appropriate amendment to the protocol is to be implemented.

All protocol amendments must be reviewed and approved in the same manner as the protocol.

## **9.4. Monitoring**

Monitoring will be conducted by regular on-site monitoring visits and inhouse data quality review. The frequency of site monitoring will be determined by assessing all characteristics of the study, including its nature, objective and methodology.

Monitors will review every subject's medical records and other source data to ensure consistency and/or identify omissions compared to the eCRF. Clinical monitoring will be performed by the Charité Research Organisation GmbH according to local SOP.

The investigator/institution will allow study-related site monitoring, audits, IRB/IEC review and regulatory inspections. Direct access must be provided to the eCRF and all source documents/data, including progress notes, copies of laboratory and medical test results, which must be available at all times for review by the CRA, auditor and regulatory inspector. They may review all eCRFs and informed consents. The accuracy of the data will be verified by direct comparison with the source documents. The sponsor will also monitor compliance with the protocol and eGCP.

## **9.5. Quality Assurance**

High scientific quality of the study will be assured through several measures. Pre-study initiation visits will be performed checking all prerequisites and established procedures and issuing reports on possible shortcomings which will have to be overcome by the study site. At the same time, extensive on-site training, especially regarding the therapeutic interventions and procedures, will be given. On regular basis, completeness and validity of data and correctness of procedures will be verified and sources of missing data will be identified by monitoring visits. Source data verification will be conducted for 100 % of subjects.

[figure not shown]

Additional quality assurance measures comprise: Plausibility checks during data entry and daily comprehensive plausibility checks on the database with active query management.

A quality assurance audit/inspection of this study may be conducted by the sponsor, sponsor's designees, or by IRB/IEC or by regulatory authorities. The quality assurance auditor will have access to all medical records, the investigator's trial-related files and correspondence, and the informed consent documentation of this clinical study.

## **9.6. Record Retention and Archiving**

The investigator is to retain and archive one copy of all data generated in the course of the study. This shall include, but not be limited to, those items defined by GCP as essential.

Records shall be retained securely and under appropriate conditions for their preservation for a minimum period of 15 years.

All study documents and drugs will be stored at the investigational site in accordance with GCP and GMP requirements. Records and documents, including signed informed consent forms, pertaining to the conduct of this trial will be retained by the investigator for 15 years after end of trial. All clinical data will be recorded, handled, and stored in a way that allows its accurate reporting. Data associated with biological samples will be transferred to laboratories in accordance with the Laboratory Manual.

## **9.7. Data Management**

For each subject screened, an electronic eCRF will be completed within the Electronic Data Capture (EDC) system and approved by the investigator.

All data entered in the eCRF will be verifiable in source documentation other than the eCRF. Source documents are filed at the trial site according to local standard operating procedure (SOP). Trained study site staff will be responsible for entering subject source data into the validated EDC system. Data captured electronically will be immediately saved to the applicable database and changes tracked to provide an audit trail. Data validation procedures will be applied by Data Management to each stage of data handling to ensure that all data are reliable and have been processed correctly.

CDASH (Clinical Data Acquisition Standards Harmonization) format will be applied to EDC setup to ensure adaptation to CDISC SDTM (Clinical Data Interchange Standards Consortium Study Data Tabulation Model).

Data Management SOPs are in place for EDC Setup, EDC User Management, Data Validation and Database Lock. The EDC database will be locked once all expected data captured in EDC, all discrepancies resolved, all external data reconciled, all medical/surgical terms and medication classified by latest versions of Medical and Drug dictionaries, all SAE reconciled with the safety database.

